## Abstract

**Background:**

Although pacemakers are primarily used for the treatment of bradycardia, diagnostic data available in current pacemakers allow them to be also used as sophisticated, continuous monitoring devices. Easy access to these stored data may assist clinicians in making diagnostic and therapeutic decisions sooner, thus avoiding potential long-term sequelae due to untreated clinical disorders. Internet-based remote device interrogation systems provide clinicians with frequent and complete access to stored data in pacemakers. In addition to monitoring device function, remote monitors may be a helpful tool in assisting physicians in the management of common arrhythmia disorders.

**Methods:**

The **P**acemaker **RE**mote **F**ollow-up **E**valuation and **R**eview (PREFER) trial is a prospective, randomized, parallel, unblinded, multicenter, open label clinical trial to determine the utility of remote pacemaker interrogation in the earlier diagnosis of clinically actionable events compared to the existing practice of transtelephonic monitoring. There have been 980 patients enrolled and randomized to receive pacemaker follow up with either remote interrogation using the Medtronic CareLink^® ^Network (CareLink) versus the conventional method of transtelephonic monitoring (TTM) in addition to periodic in-person interrogation and programming evaluations. The purpose of this manuscript is to describe the design of the PREFER trial. The results, to be presented separately, will characterize the number of clinically actionable events as a result of pacemaker follow-up using remote interrogation instead of TTM.

**Trial registration:**

ClinicalTrials.gov: NCT00294645.

## Background

Pacemaker therapy is indicated to treat bradycardia due to sinus node or atrioventricular conduction disorders. In addition to pacing, current devices have expanded recording and diagnostic capabilities, providing continuous cardiac monitoring and long-term trended clinical information. Pacemakers can store atrial as well as ventricular high rate episodes, along with percentage of atrial and ventricular pacing, capture management data, and many other clinically useful parameters. Furthermore, the atrial high rate diagnostic data in pacemakers have been shown to have good sensitivity and specificity for the diagnosis of atrial fibrillation (AF) [1,2]. Pacemaker therapy monitoring is most frequently achieved in the United States with a combination of in-person programming evaluations and transtelephonic monitoring (TTM). TTMs are primarily used to monitor battery status, and are performed at a frequency adjusted as implant duration progresses. TTMs, however, have no ability to download the monitored data stored in pacemakers. Full device data interrogations are only available through in-person programming evaluations.

The advent of internet-based remote monitoring systems allow for full device interrogation while the patient is in their home or other remote location. This allows clinicians to have more frequent and complete access to the device data without creating a substantial burden on the patient and the clinician with increased office visits. In addition to the Medtronic CareLink^® ^Network (CareLink) (Minneapolis, MN, USA), remote monitoring systems are also available through Biotronik Home Monitoring (Berlin, Germany), St. Jude Housecall™ (St. Paul, MN, USA), and Boston Scientific Latitude^® ^(St. Paul, MN, USA). The functionality of these systems has been well described for use in patients with implantable cardioverter-defibrillators (ICD). Clinically significant findings such as ventricular tachycardia [3], silent AF [4], early volume overload [5], and lead fractures causing inappropriate shocks [6] have been detected during clinicians' reviews of the remote transmissions. Remote monitoring systems, however, have not been described for use in patients with pacemakers.

The purpose of the PREFER trial is to evaluate the utility of systematic remote interrogation to monitor pacemaker and patient condition in order to increase the awareness of physicians to any events which may necessitate early clinical intervention.

## Methods/Design

### Hypothesis

The PREFER trial examines the hypothesis that quarterly device monitoring by remote interrogation will result in the earlier diagnosis of clinically actionable events compared to the combination of TTM and routine office visits.

### Primary endpoint

The primary endpoint is the rate of first diagnosis of clinically actionable events in patients whose pacemakers are followed by remote interrogation versus those whose pacemakers are followed by office visits augmented by TTM. The goal of early identification of clinically actionable events is to have early intervention by a clinician, which could impact the clinical sequelae. The clinically actionable events were selected on the basis that their presence merits a clinical decision or further medical assessment. Clinically actionable events are defined as:

• Atrial tachycardia (AT)/AF episodes ≥ 48 hours (defined as two consecutive days in which the device records at least 18 hours of AT/AF per day)

• Ventricular pacing that has increased by 30 percent relative since last device interrogation

• Sensed ventricular rate of ≥ 100 bpm during atrial arrhythmia for at least 20 percent of the time since previous device interrogation

• Non-sustained ventricular tachycardia (NSVT) ≥ 5 beats

• New onset AT/AF in patients with no prior history of AT/AF

• Loss of capture

• Increase in pacing voltage threshold ≥ 1 V

• Significant changes in atrial or ventricular lead impedance, defined as:

◦ < 200 of > 2000 ohms

◦ Unstable lead impedance deemed to be clinically actionable

◦ ≥ 50 percent change in lead impedance since last interrogation

• Elective Replacement Indicator (ERI) or End of Life (EOL)

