### Randomization

Patients were randomized 2:1 to remote interrogation at three month intervals or TTM evaluations at two month intervals. A permutated block randomization was used to randomize the subjects. Patients who were randomized to follow up with the remote interrogation will transmit pacemaker information at 3, 6, and 9 months after enrollment and have an office visit at 12 months post-enrollment. The TTM control subjects with single chamber devices will transmit 30 second TTM strips with and without magnet application at 2, 4, 6, 8, and 10 months after enrollment and have an office visit at 12 months. Patients with dual chamber devices will transmit via TTM at 2, 4, 8, and 10 months after enrollment, with office visits at 6 and 12 months post enrollment. The frequency of TTM transmissions is the maximal permitted under Centers for Medicare and Medicaid Services (CMS) reimbursement guidelines [7] and reflective of average frequency of TTM transmissions from Medicare patients. The trial design flowchart is shown in Figure 1.

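### Three primary-endpoint criteria are judged against the previous interrogation, which by schedule lies 3 months back in the remote arm and 6 or 12 months back in controls

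*Protocol article*

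**What the plan says.** The Primary endpoint section lists nine components. Three contain a criterion whose reference is the last or previous interrogation:

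- "Ventricular pacing that has increased by 30 percent relative since last device interrogation";
- a sensed ventricular rate of 100 bpm or more during atrial arrhythmia, "for at least 20 percent of the time since previous device interrogation";
- within the lead-impedance component, "≥ 50 percent change in lead impedance since last interrogation" (one of three sub-criteria).

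The Randomization section gives the schedules: "Patients were randomized 2:1 to remote interrogation at three month intervals or TTM evaluations at two month intervals". Remote-arm patients "will transmit pacemaker information at 3, 6, and 9 months after enrollment and have an office visit at 12 months post-enrollment". Single-chamber controls send TTM strips "at 2, 4, 6, 8, and 10 months after enrollment and have an office visit at 12 months". Dual-chamber controls have office visits at months 6 and 12, with TTM at months 2, 4, 8 and 10.

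The Background section settles whether a TTM contact counts as an interrogation: "TTMs, however, have no ability to download the monitored data stored in pacemakers". It adds that full interrogation otherwise needs an in-person evaluation.

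The primary analysis pools all components into one time-to-first-diagnosis comparison. The article states no common look-back window and no fixed reference visit.

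**The concern.** The Hypothesis section claims earlier diagnosis. That presupposes an event which both arms could in principle record, seen sooner in one of them. It holds for criteria with a fixed definition, such as AT/AF of 48 hours or more, NSVT, or ERI/EOL. It does not hold for a criterion whose reference point moves with the visit schedule, because the schedule is what was randomized. The same course in the same patient can then meet the criterion in one arm and never meet it in the other, even at the shared 12-month visit, where the two arms look back to different dates.

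At stake is the interpretation of the primary result. A difference in time to first diagnosis may mix earlier detection with a different rule for what counts. The Peto & Peto test gives more weight to early differences, so extra remote-arm events at month 3 would weigh heavily.

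**Working it through.** The planned 700 subjects come from simulations whose event rates the article does not print. That figure cannot be reproduced, and nothing below depends on it.

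**Inputs.** Visit schedules are from Randomization, the status of TTM from Background, and the thresholds from Primary endpoint. I assume that the baseline visit and each office visit include an interrogation and that there are no unscheduled ones.

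**Step 1: the look-back.**

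| Follow-up | Interrogations (month) | Look-back | Month-12 reading refers to |
|---|---|---|---|
| Remote | 3, 6, 9, 12 | 3 months | month 9 |
| Control, dual-chamber | 6, 12 | 6 months | month 6 |
| Control, single-chamber | 12 | 12 months | baseline |

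**Step 2: a temporary rise in pacing (threshold +30% relative).** Assume 20% at baseline, 30% throughout the first quarter and 20% afterwards. The article does not say whether the percentage read is a point value or an average since the last interrogation, so both are shown.

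- Remote, month 3: 30/20 − 1 = +50% on either reading. Event.
- Dual-chamber control, month 6: point value 20/20 − 1 = 0%; average (30 + 20)/2 = 25, and 25/20 − 1 = +25%. Month 12: 0% (point) or 20/25 − 1 = −20% (average). Never an event.
- Single-chamber control, month 12: point value 0%; average (30 + 20 + 20 + 20)/4 = 22.5, and 22.5/20 − 1 = +12.5%. Never an event.

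**Step 3: the opposite direction.** Assume pacing doubles in a straight line over the year, from 20% to 40%.

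- Remote, point values 20, 25, 30, 35, 40: rises of 25.0%, 20.0%, 16.7% and 14.3%. Quarterly averages 22.5, 27.5, 32.5, 37.5 against a baseline of 20: rises of 12.5%, 22.2%, 18.2% and 15.4%. Never an event.
- Dual-chamber control: point values 20, 30, 40 give +50% at month 6. Half-year averages 25 and 35 give +25%, then 35/25 − 1 = +40% at month 12. Event on either reading.
- Single-chamber control, month 12: +100% (point) or 30/20 − 1 = +50% (average). Event on either reading.

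The schedule can therefore add or remove events in either arm.

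**Step 4: the 20% rule.** The threshold in days is 0.20 × 91.3 = 18.3 over 3 months, 0.20 × 182.6 = 36.5 over 6 and 0.20 × 365.25 = 73.1 over 12. Take 25 days' worth of fast rate (25 × 24 = 600 hours) in the first quarter and none later: 25/91.3 = 27.4%, 25/182.6 = 13.7% and 25/365.25 = 6.8%. If those hours are continuous, the AT/AF criterion of 48 hours is met in every arm, so the composite is not affected. Suppose instead they are spread as 10 hours a day over 60 days, with total AT/AF below 18 hours on each day, in a patient with prior AT/AF. Then neither AT/AF criterion applies, and the rule is met only on the 3-month schedule.

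**Step 5: impedance change of 50%.** 1.5^(1/2) = 1.225 and 1.5^(1/4) = 1.107. A steady rise of 22.5% per quarter reaches +50% over 6 months, and one of 10.7% per quarter reaches it over 12 months. Neither reaches it at any 3-month look. The other two impedance sub-criteria could still catch such a change.

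**The case against.** **Interrogation frequency is the intervention.** The Analysis of primary objective section limits its conclusion to follow-up as conducted in the trial. This stands: as a comparison of two strategies the test is valid. It does not carry over to the Hypothesis section, which speaks of earlier diagnosis.

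**A reader might infer that a 25-day fast-rate burst counts in the remote arm and never in controls.** The document does not support this for the composite. A continuous burst during atrial arrhythmia already meets the criterion of two consecutive days with at least 18 hours of AT/AF. If the hours are instead spread evenly through the year, the percentage is the same over 3, 6 or 12 months. Only an uneven, interrupted pattern, as in Step 4, is affected.

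**A reader might infer that slow drift from 20% to 30% pacing over a year is an event in single-chamber controls only.** With point values it is +50% at month 12. With interval averages the year averages about 25%, which is +25% and no event. The article does not settle which reading applies, so I do not rely on this example. Steps 2 and 3 hold on both readings.

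**Single-chamber devices.** The article does not say that the 20% rule applies to them, so the 73.1-day and 6.8% figures are conditional. The contrast of 3 with 6 months is not.

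**Each component is also analysed separately.** That helps in part, but separate tests do not give the time to the first of the remaining events, which is what is needed to judge the composite.

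**Conclusion.** For three criteria in three of the nine components, and for impedance in only one of three sub-criteria, the randomized schedule affects whether an event exists as well as when it is seen. The clearest case is the temporary pacing rise: +50% at month 3 in the remote arm, against at most +25% or +12.5% in controls, where the threshold is +30%.

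It would go too far to say that the arms have different primary endpoints, or that a positive result could not reflect earlier diagnosis. Criteria with fixed definitions are not affected, the bias can run either way, and without component event rates its direction and net size cannot be computed.

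The conclusion rests on interrogations occurring as scheduled, including one at baseline, which the Design section does not list explicitly. Unscheduled interrogations would shorten individual look-backs. The reference for the 1 V rise in pacing threshold is not stated; if it is also the last interrogation, that criterion has the same problem.

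**What to change.** Before analysis, pre-specify a time-to-first-diagnosis analysis of the composite without the three interval-dependent criteria, using the same test as the primary analysis. Report it beside the primary result, and attribute a difference to earlier diagnosis only if it persists there. If it does not persist, describe the primary result as a difference between follow-up strategies in recorded events. State the reference for the 1 V criterion and, if it is the last interrogation, leave that criterion out as well.

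Where a baseline interrogation value is available, also report the pacing and impedance criteria judged against baseline in both arms. This can only be supportive, because the primary endpoint counts clinician-diagnosed events, which a later derivation cannot fully replace. I would not convert the 20% rule to a fixed number of days: 18.3 days over a year is 18.3/365.25 = 5.0% of the time, which is a different criterion.

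The main supporting analysis needs only each event's type and date, and no change to the conduct of the trial. The cost is a little more analysis work and fewer events, hence less power, in that analysis.

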### Secondary endpoints

The first secondary endpoint of the trial is to characterize the frequency of actions for each of the clinically actionable events defined above. There are nine additional secondary objectives; each assesses the contribution of individual clinically actionable events to the primary objective.

### Design

The PREFER trial is a prospective, randomized, parallel, unblinded, multicenter, open label clinical trial to investigate the clinical value of remote interrogation in the management of patients with pacemakers. All study patients received a Medtronic Kappa^® ^900, EnPulse^®^, Adapta™, or Versa™ device supported by CareLink. The pacemakers are either single- or dual-chamber devices. Fifty investigative centers in the United States (US) enrolled a total of 980 patients between May 2004 and March 2007, with planned 12-month follow up.

The primary inclusion criteria are:

◦ Patient is at least 30 days post system modification, including new device implant, device upgrade, or lead changes.

◦ Patient has access to an analog phone line.

◦ Patient is capable of operating the TTM monitor and the CareLink Monitor.

The exclusion criteria are:

◦ Enrollment in another pacemaker clinical study that might confound the results of this trial.

◦ Patient is a candidate for an ICD.

All patients who met eligibility requirements and signed an Institutional Review Board (IRB) approved PREFER trial Informed Consent Form and an Authorization for the Use and Disclosure of Health Information underwent an in-office baseline evaluation to quantify baseline characteristics. Baseline evaluations included pacemaker information, cardiovascular medical and surgical history, New York Heart Association (NYHA) classification, and arrhythmia history.

### Randomization

Patients were randomized 2:1 to remote interrogation at three month intervals or TTM evaluations at two month intervals. A permutated block randomization was used to randomize the subjects. Patients who were randomized to follow up with the remote interrogation will transmit pacemaker information at 3, 6, and 9 months after enrollment and have an office visit at 12 months post-enrollment. The TTM control subjects with single chamber devices will transmit 30 second TTM strips with and without magnet application at 2, 4, 6, 8, and 10 months after enrollment and have an office visit at 12 months. Patients with dual chamber devices will transmit via TTM at 2, 4, 8, and 10 months after enrollment, with office visits at 6 and 12 months post enrollment. The frequency of TTM transmissions is the maximal permitted under Centers for Medicare and Medicaid Services (CMS) reimbursement guidelines [7] and reflective of average frequency of TTM transmissions from Medicare patients. The trial design flowchart is shown in Figure 1.

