### Statistical methods and data analysis

#### Sample size methods and assumptions

Data from the Atrial High Rate (A-HIRATE) study were used to estimate the survival rates for patients in each arm of the PREFER trial. The A-HIRATE study evaluated pacemaker patients implanted with a Kappa 700 or Kappa 900 device [8]. Due to device diagnostic limitations of the Kappa 700, only the 157 subjects in the A-HIRATE study that were implanted with a Kappa 900 device and followed through at least one month post-implant were used for event rate estimation, as this most closely approximates patients in the PREFER trial.

Simulations were used to determine the sample size necessary to evaluate the primary objective while following patients through quarterly remote interrogations compared to the combination of TTM transmissions and in-office visits, while achieving 80 percent power and α = 0.05. A sample size requirement of 700 subjects was determined.

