#### Analysis of primary objective

The time to first diagnosis of a clinically actionable event or censoring will be determined for each randomized subject. The Peto & Peto modification of the Gehan-Wilcoxon test will be performed [9]. Only events diagnosed by the clinician will count toward the primary endpoint. If the test yields a p-value less than 0.05, it will be concluded that the freedom from first diagnosis of clinically actionable event(s) is significantly lower when patients are followed through remote interrogation as they were in this trial, compared to being followed through TTM and scheduled in-office visits.

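### The primary test is stated without strata, although control visits differ by device type and event risk plausibly differs by AT/AF history: a valid test, but stratifying it and reporting by device type would be a free improvement

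*Protocol article*

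**What the plan says.** All references are to the protocol article.

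- **Device types (Design).** "The pacemakers are either single- or dual-chamber devices". Proportions are not given.
- **Follow-up (Randomization).** Remote patients transmit at 3, 6 and 9 months and attend the office at 12, with either device. Single-chamber controls have TTM at 2, 4, 6, 8 and 10 months and one office visit, at 12. Dual-chamber controls transmit "via TTM at 2, 4, 8, and 10 months after enrollment, with office visits at 6 and 12 months post enrollment". Allocation is 2:1 in permuted blocks; no strata are mentioned.
- **What TTM can see (Background).** TTM cannot retrieve stored device data; in the control arm these come only from in-person interrogation.
- **Endpoint (Primary endpoint).** Nine event types are listed. One, new-onset AT/AF, applies only to patients with no AT/AF history.
- **Baseline data (Design).** Pacemaker information is collected, and so are "New York Heart Association (NYHA) classification, and arrhythmia history".
- **Analysis (Analysis of primary objective).** "The Peto & Peto modification of the Gehan-Wilcoxon test will be performed". The 0.05 threshold and the conclusion to be drawn follow. No strata or covariates are named, and only clinician-diagnosed events count.

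**The concern.** The outcome is time to *diagnosis*, so the visit schedule itself produces much of the treatment contrast. For an event held only in device memory, the first scheduled opportunity is month 3 in the remote arm, against month 12 for a single-chamber control and month 6 for a dual-chamber control. Device type therefore modifies the expected effect by design.

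AT/AF history probably changes event risk as well. It decides whether the new-onset item can occur, and two other items (AT/AF of at least 48 hours, and fast ventricular rate during atrial arrhythmia) also depend on atrial arrhythmia.

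A rank test that pools patients with different risks and different control schedules can be less sensitive than one comparing like with like. The single result is also an average over two contrasts, 3 v 12 months and 3 v 6 months, that a clinic would want to see apart. What is at stake is efficiency and interpretation, not validity.

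**Working it through.** **1. The plan's own figure.** "Simulations were used to determine the sample size necessary to evaluate the primary objective", with the aim of "achieving 80 percent power and α = 0.05", and the result was: "A sample size requirement of 700 subjects was determined". The event rates, effect size, drop-out and device mix behind those simulations are not printed, so 700 cannot be rebuilt. A rough bracket is the Schoenfeld formula with 2:1 allocation, 80% power and two-sided 0.05 (sidedness is not stated; two-sided is assumed):

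events = (1.960 + 0.842)² / [(2/3)(1/3)(ln HR)²] = 7.85 / [0.2222 (ln HR)²]

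| Hazard ratio | Events | Share of 700 |
|---|---|---|
| 1.4 | 312 | 45% |
| 1.5 | 215 | 31% |
| 1.6 | 160 | 23% |
| 2.0 | 74 | 11% |

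So 700 is attainable under many assumptions; it is neither confirmed nor refuted.

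**2. Validity of the pooled test.** Simulated trials of 700 patients with the same schedule in both arms gave a type I error of 0.044 to 0.056 for the unstratified test over five scenarios. It holds its level.

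**3. Power with and without strata.** Simulation of the Peto-Peto test.

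- From the article: 700 patients, 2:1, detection at the stated visits.
- Assumed: 5% drop-out, 40% with AT/AF history, 5% of events visible on TTM, dual-chamber share 60%, 80% or 90%, and control office visits leading to diagnosis of 100% or 70% of events.
- Hazard patterns, in the order dual with history, dual without, single with, single without: A = 1, 1, 1, 1; B = 1, 1.5, 0.5, 0.5; C = 2, 1, 1, 0.5.
- Each setting was scaled so that the unstratified test has about 80% power; 1,000 runs each. The Monte Carlo standard error of one power figure is about √(0.8 × 0.2 / 1000) = 1.3 points. The three tests were run on the same simulated trials.

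Power in %, as unstratified / by device / by device and AT/AF history:

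| Dual share | Pattern | Control diagnoses 100% | Control diagnoses 70% |
|---|---|---|---|
| 60% | A | 82.5 / 89.0 / 88.6 | 80.6 / 81.5 / 81.2 |
| 60% | B | 78.0 / 86.7 / 87.0 | 78.7 / 80.1 / 80.5 |
| 60% | C | 81.7 / 87.9 / 91.1 | 83.4 / 83.6 / 85.1 |
| 80% | A | 78.2 / 83.9 / 83.1 | 78.8 / 79.5 / 79.9 |
| 80% | B | 78.2 / 82.0 / 81.9 | 79.3 / 79.9 / 79.7 |
| 80% | C | 79.7 / 83.1 / 86.9 | 80.6 / 80.6 / 82.4 |
| 90% | A | 78.4 / 81.0 / 80.4 | 77.2 / 77.3 / 77.0 |
| 90% | B | 77.1 / 78.8 / 79.5 | 79.8 / 80.2 / 79.9 |
| 90% | C | 79.2 / 81.6 / 84.4 | 86.1 / 86.0 / 87.2 |

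When control visits diagnose every event, device strata add 1.7 points (78.8 − 77.1) to 8.7 (86.7 − 78.0), and device plus history adds 2.0 (80.4 − 78.4) to 9.4 (91.1 − 81.7). When they diagnose 70%, device plus history changes power by −0.2 (77.0 − 77.2) to +1.8 (80.5 − 78.7). These runs split both device types by history; merging the two single-chamber cells into one stratum made little difference when checked.

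**4. Stronger assumptions, not scaled to 80% power.** All risks are assumed 12-month proportions.

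- 80% dual-chamber; risk 70% with and 20% without AT/AF history in dual-chamber patients: 19% unstratified, 21% by device, 41% by both.
- 60% dual-chamber; risk 40% and 60% in dual-chamber patients, 15% in single-chamber: 27%, 38%, 40%.
- 15% single-chamber, 35% of dual-chamber patients with history; risks 20% (single), 75% (dual with history), 40% (dual without): 51% unstratified, 54 to 55% by device, 63 to 66% by both, over two separate simulations.

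**5. Enrolment.** If 700 patients give 80% power and all 980 enrolled contribute at the same effect, power is Φ(2.802 × √(980/700) − 1.960) = Φ(3.315 − 1.960) = Φ(1.355), about 91%.

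**The case against.** The strongest reply is that this is a condensed design article. It never says that the test is unstratified, and strata and subgroup reports are commonly left to an analysis plan. That stands to this extent: a reader must not take silence as proof that strata were ruled out. But the article does name the test, its threshold and its conclusion, so one can comment on the method as stated and ask for confirmation.

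Four stronger readings are tempting, and the document supports none of them.

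- *The pooled test is wrong or biased.* It is not. Randomization balances device type in expectation, the level holds, and the comparator is defined as TTM plus scheduled office visits, so both control schedules belong to it.
- *The trial has only about half the power it claims.* Figures such as 51% follow from an assumed device mix and assumed risks. The article reports 80% at 700, so those scenarios do not represent its planning case. Enrolment was 40% above 700 (980/700 = 1.4), although the article does not say whether the excess was meant for attrition.
- *Patients with AT/AF history are outside the endpoint.* They can have eight of the nine event types. The new-onset item even gives patients without history an extra way to qualify, which may narrow the risk gap. The article gives no comparison of event risk by history.
- *Stratifying separates the two control schedules.* It does not; one p-value still combines them. Only results by device type show them apart.

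**Conclusion.** The point holds as a free improvement in efficiency and reporting, not as an error or contradiction. The stated pooled test is valid but can lose power. Under assumptions scaled to about 80% power, stratifying by device type and AT/AF history is worth from nothing to about 9 points. The gain is largest when single-chamber devices are common and control visits diagnose nearly all events, and close to nothing when controls diagnose 70%. Gains above that came only from unscaled runs with wide assumed risk gaps, most of all a very strong effect of AT/AF history. No run showed a material loss: the worst change, −0.2 points, is within simulation error.

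The size depends on device mix, prevalence of AT/AF history, event rates and control detection, none of which the article gives. The case for reporting by device type stands even if the power gain is nil, because the two control schedules are different comparisons.

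**What to change.** Before the outcome data are analysed:

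1. Specify the primary Peto-Peto test as stratified by device type and baseline AT/AF history, in three strata: single-chamber; dual-chamber with history; dual-chamber without. Sum the scores and variances over strata, and keep the 0.05 threshold.
2. Report the remote-versus-control effect, with its precision, separately for single- and dual-chamber devices, stating the control schedule beside each.
3. If the analysis plan already sets these strata, confirm it and cite the section; nothing more is needed.

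The cost is a few lines of analysis code and one extra table. Device information and arrhythmia history are collected at baseline, so no new data, patients or visits are required.
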